## Abstract

**Background/Objectives:** Sepsis and septic shock are the most severe forms of infection. Due to the intensive cross-talk of the coagulation and immune system, coagulopathies regularly occur in sepsis. The International Society on Thrombosis and Hemostasis refers to these coagulation abnormalities as sepsis-induced coagulopathies (SICs). The presence of SICs can be assessed using the SIC score. In parallel, a score for “sepsis-associated coagulopathy” (SAC) was introduced that, in contrast to the SIC score, allows coagulopathy to be classified according to its severity. In the past, multicenter, randomized controlled trials have repeatedly failed to prove the efficacy of specific therapeutic measures targeting SICs or SACs. This could potentially be explained by insufficient knowledge about the prevalence and incidence of SIC and the rate of spontaneous recovery. The Incidence of Sepsis-Induced Coagulopathy (INSIC) trial is intended to address this problem. **Methods:** The aim of the INSIC trial is to measure the incidence and prevalence of SIC—in addition to the rate of spontaneous SIC recoveries—during the first days of sepsis treatment to provide a solid base of data for future interventional trials. We aim to include all patients with sepsis treated in any one of 150 participating intensive care units in 100 hospitals located in Austria, Luxembourg, and Germany to determine the prevalence of SIC (on day 1 of the study period as well as on three selected days in the fourth quarter of each year from 2019 to 2024). SIC incidence will be assessed over a 14-day period starting on 10 March 2025. Secondary endpoints are 28-day survival and the occurrence of severe thromboembolic events and bleeding. In addition, each of the aforementioned outcome parameters will be assessed for correlation with the severity classification of the SAC score. **Conclusions:** The INSIC trial is the first study to determine the prevalence as well as the incidence of SIC, to prospectively examine the course of SIC longitudinally over a 14-day period, and to determine the rate of spontaneous recoveries within 72 h under standard treatment in a large cohort of patients. This information will provide a sound basis for future studies.

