### 1.1. Objectives

The primary outcome of the INSIC trial is the SIC incidence rate within a 14-day observation period (new cases/1000 ICU days). Moreover, we aim to determine the point prevalence of SIC on day 1 of the study period and on three reference days in the fourth quarter of each year from 2019 to 2023. The secondary outcome parameters are as follows: (I) length of stay in intensive care unit (ICU) until transfer to a normal ward; (II) ICU mortality rate (in all patients and in subgroups of patients with sepsis, septic shock, and SIC according to the different scores); (III) 28-day hospital mortality rate (in all patients and in subgroups of patients with sepsis, septic shock, and SIC according to the different scores); (IV) SIC recovery rate 72 h after SIC onset; (V) thromboembolic events after sepsis onset (in sepsis, septic shock, or SIC) up to day 28, death, or hospital discharge (whichever occurs first); and (VI) relevant bleeding without surgical trauma (non-trauma or surgery-related major bleeding causing a drop in hemoglobin of <1 g/dL) after the onset of sepsis (in sepsis, septic shock, or SIC) until day 28, death, or hospital discharge (whichever occurs first). (VII) Each of the above-mentioned outcome parameters will also be tested for correlation with the different degrees of severity of SAC (according to the SAC score) (Table 1), which allows for a more differentiated assessment of the severity of coagulopathy.

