### 2.4. Outcomes

The primary outcome parameters of the INSIC trial are as follows:
(1)The incidence rate of SIC within a 14-day observation period (new cases/1000 patient days).(2)The point prevalence of SIC on day 1 of the study period and on three reference days in the 4th quarter of each year from 2019 to 2023.

The secondary outcome parameters of the INSIC trial are as follows:
(1)Length of stay in the ICU until transfer to a normal ward.(2)ICU mortality rate (in all patients and in the subgroups of patients with sepsis, septic shock, SIC, or SAC (mild, moderate, severe) according to the different scores).(3)Mortality rate until day 28, hospital death, or hospital discharge (whatever occurs first, in all patients and in the subgroups of patients with sepsis, septic shock, SIC, or SAC (mild, moderate, severe) according to the different scores).(4)SIC and SAC (mild, moderate, severe) recovery rate 72 h after SIC or SAC onset. The time point was chosen as the 72 h period reflects a critical window during which early death in sepsis or a clinical response to sepsis therapy can be expected [15].(5)Thromboembolic events after sepsis onset (in sepsis, septic shock, SIC, or SAC (mild, moderate, severe)) up to day 28, death, or hospital discharge (whichever occurs first).(6)Relevant bleeding without surgical trauma (hemoglobin loss >1 g/dL within 24 h, due to bleeding rather than dilution) after sepsis onset (in sepsis, septic shock, SIC, or SAC (mild, moderate, severe)) until day 28, death, or hospital discharge (whichever occurs first).

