### 2.5. Procedure and Data Collection

We will collect general structural data (see Figure 1) for each participating study center. All patients treated in the participating ICUs in a 14-day period will be included. Notably, only data generated in the context of standard patient care will be collected. For each patient treated in the participating ICUs, the following data will be collected: gender, age, date and time of hospital admission, referring ward or hospital (if applicable), Simplified Acute Physiology Score (SAPS) II, date and time of hospital discharge, patient status at discharge (alive, dead, returning home, or going to a care facility). In addition, for each patient we intend to collect data describing the dates and times of ICU admission and discharge as well as the type of admission (surgery—planned or emergency; medical treatment—planned or emergency) and the survival status at ICU discharge.

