For each patient diagnosed with sepsis or septic shock during the observation period, more detailed information will be collected (date and time of sepsis onset, date and time of septic shock onset, infectious focus, causative pathogen(s), and secondary infections (super- and/or nosocomial infections and/or infections of a further organ system)). Furthermore, investigators will be asked to extract data from the hospital information system describing additional patient characteristics. These include the American Society of Anesthesiologists (ASA) classification [16], the Revised Cardiac Risk Index (RCRI) [17] score, the status of and, if applicable, the reason for pre-existing anticoagulation therapy or antiplatelet therapy, coagulopathy, and severe liver disease. Furthermore, information on past episodes of heparin-induced thrombocytopenia (HIT) type II will be collected. For all patients hospitalized with sepsis in the ICU on the first day of the observation period, it will be determined whether SIC was present before the start of the observation period. Furthermore, for each patient diagnosed with sepsis or septic shock during the observation period, on the day of sepsis diagnosis (day 0), on days 1–4, and on the day of sepsis discharge, the following measures will be collected: the sequential sepsis-related organ failure assessment (SOFA) score [2], the international normalized ratio (INR), and platelet count. For further exploratory analyses, the following parameters are recorded where available: anti-factor Xa activity, activated partial thromboplastin time (aPTT), prothrombin time, D-dimer level, fibrinogen concentration, thrombin–antithrombin complex (TAT) concentration, thrombin fragment F1.2 concentration, and measures from thrombelastometric testing. Likewise for exploratory analyses, the following parameters are collected: the levels of inflammation markers (C-reactive protein (CRP), procalcitonin (PCT), and interleukin-(IL) 6), as well as the dose of anticoagulant administered, the amount of fluid infused (per day), the amount of blood products transfused (per day), and the administered amount of coagulation factors and desmopressin (per day), determined at the same time points. Using the collected data and the SIC scores, all patients with sepsis will be tested for SIC at least once a day. Additionally, SIC scores (exact scores) will be recorded daily until day 14 after sepsis onset or discharge from the ICU (whatever occurs first). The date and time of the first SIC occurrence will be registered. The data collected will also be used to calculate the severity of SAC, according to Lyons et al. [6]. Finally, until day 14 after the onset of sepsis, each patient will be checked for thromboembolic events and non-trauma or surgery-related major bleeding (causing a drop in hemoglobin of <1 g/dL) once a day. In addition, on the 28th day after sepsis onset, it will be determined whether cardiovascular events, thromboembolic events, or non-trauma or surgery-related major bleeding (causing a drop in hemoglobin of <1 g/dL) occurred during the second 14 days of follow-up monitoring (yes/no recording for the second 14 days). Figure 2 provides an overview of the planned timeline. The time frames were chosen on the basis of balancing efforts and benefits. Since it is currently assumed that SIC occurs in the early phase of sepsis due to a dysregulation of the interaction of the innate immune response with the coagulation system, a special focus was placed on the first days, i.e., day 0 (sepsis onset) and the following 4 days. The aim is to identify possible early warning signs of SIC. Sepsis is usually treated anti-infectively for 7–14 days. The first occurrence of SIC after day 14 was considered very unlikely. The experts involved in the study planning were of the opinion that the occurrence of SIC after day 14 was most likely due to a secondary infection (which triggers a new sepsis episode) or another sepsis-independent reason. It was decided to use the 28-day mortality rate, as it is frequently collected in sepsis studies and thus allows an approximate comparison of the mortality of this cohort with other study cohorts. In the aforementioned effort to balance efforts and benefits, it was decided to investigate the potential effects of SIC on thromboembolism and bleeding risk up to day 28.

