### 2.10. Statistical Methods

All patients who do not have SIC at the beginning of their individual observation period will be included in the calculation of the cumulative observation period for determining the incidence rate of SIC. The observation period for determining the incidence rate of SIC ends at the time of diagnosis of SIC or discharge from the ICU (depending on which event occurs first), but at the latest at the end of the 14-day observation period. The incidence rates for sepsis and septic shock are determined in the same way. To determine the incidence density, the number of incident patients is divided by the cumulative sum of the individual observation days of all patients included in the incidence calculation. The incidence density is thus calculated according to the following formula:$$\frac{\mathrm{Number}\;\mathrm{of}\;\mathrm{incidental}\;\mathrm{cases}}{\begin{array}{l} \mathrm{Sum}\;\mathrm{of}\;\mathrm{the}\;\mathrm{individual}\;\mathrm{observation}\;\mathrm{period}\;\mathrm{across}\;\mathrm{all}\;\mathrm{cases} \end{array}}$$

The corresponding 95% confidence interval is calculated based on a Poisson distribution. The incidence rates between the individual strata will be compared in pairs.

The point prevalences for SIC, sepsis, and septic shock will be determined on the first day of the observation period by calculating the ratio of the number of affected patients to the total number of patients in the ICUs on that day. The Wilson score method will be used to determine the associated 95% confidence interval. Using χ^2^ tests (or Fisher’s exact tests), the point prevalences of the individual strata will be compared. The prevalences of SIC, sepsis, and septic shock in the retrospective data collection will be determined analogously.

The available data will be described by specifying the median [interquartile range (IQR)] or the absolute (relative) frequency. Depending on the type of characteristic being analyzed, the different groups will be compared using the χ^2^ test (or Fisher’s exact test, if necessary), the Mann–Whitney U test, or the *t*-test. The Kaplan–Meier method will be used to determine survival times, and the log-rank test will be used for the relevant group comparisons.

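### Kaplan–Meier and log-rank are prescribed for a mortality outcome that ends at hospital discharge, with no competing-risk method; under ordinary use the curves would overstate in-hospital mortality and the unadjusted SIC contrast would be blurred

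*Protocol article*

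**What the plan says.** All references are to the protocol article.

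- **Outcome.** Section 2.4, secondary outcome 3, reads "Mortality rate until day 28, hospital death, or hospital discharge (whatever occurs first". Section 1.1 names the same outcome "28-day hospital mortality rate (in all patients and in subgroups of patients with sepsis, septic shock, and SIC according to the different scores".
- **Data.** Section 2.5 collects "date and time of hospital discharge, patient status at discharge (alive, dead, returning home, or going to a care facility", from routine care only. It describes no check of vital status after discharge.
- **Time-to-event method.** Section 2.10: "The Kaplan–Meier method will be used to determine survival times, and the log-rank test will be used for the relevant group comparisons". It gives no rule for patients discharged alive and names no competing-risk method.
- **Other mortality analyses.** Section 2.10 also provides relative frequencies with χ² or Fisher tests, a logistic model for mortality, and a multivariate logistic model for the adjusted comparison of SIC-positive and SIC-negative patients.
- **Naming.** The abstract says "Secondary endpoints are 28-day survival", without mentioning discharge. Section 2.5 says "It was decided to use the 28-day mortality rate, as it is frequently collected in sepsis studies" and gives as the reason that this "allows an approximate comparison of the mortality of this cohort with other study cohorts".

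**The concern.** Kaplan–Meier estimates risk correctly only if patients who leave observation have the same later risk of death as those who remain. Live discharge breaks this: patients leave because they are better, and an in-hospital death can no longer occur. If they are censored at that point, the curve estimates mortality in a hypothetical hospital that discharges nobody, which is higher than the proportion who actually die in hospital.

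The log-rank test would then compare death hazards among patients still in hospital. Section 1 associates SIC with higher morbidity, so slower discharge of SIC patients is plausible. Slower discharge keeps more survivors at risk in the SIC group and lowers its hazard relative to the SIC-negative group. A real excess of in-hospital deaths in SIC could look smaller in the curves and the log-rank test than in the logistic model reported beside them.

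**Working it through.** **1. The plan's own figures.** The article gives no mortality rate, discharge rate or hazard ratio. It does give patient numbers (sections 2.7 and 2.10 give the only sizing and analysis text), and these reproduce. Scaling the INSEP study by 14/28 days and 150/133 ICUs gives a factor of 0.564, and 1500 × 0.564 = 846 sepsis patients (stated: around 850). Then 30–60% of 850 is 255–510 with SIC (stated: 250–500). For the comparison below I take the midpoint, 375 with SIC and 850 − 375 = 475 without.

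**2. Model (assumption).** Constant hazards of in-hospital death and live discharge to day 28. Let D be the share dead in hospital by day 28 and R the share discharged alive by day 28.

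- Cumulative total hazard: H = −ln(1 − D − R)
- Cumulative death hazard: H_D = H × D/(D + R)
- Mortality read from Kaplan–Meier censored at discharge: 1 − exp(−H_D)

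Example with D = 0.30, R = 0.20: H = −ln 0.50 = 0.693; H_D = 0.693 × 0.60 = 0.416; 1 − exp(−0.416) = 34.0%, against a true 30%.

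**3. Kaplan–Meier mortality at day 28 over a range of assumed rates**

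| True in-hospital death | R = 20% | R = 30% | R = 40% | R = 50% |
|---|---|---|---|---|
| 20% | 22.5% | 24.2% | 26.3% | 29.1% |
| 30% | 34.0% | 36.8% | 40.3% | 45.3% |
| 40% | 45.7% | 49.7% | 55.3% | 64.1% |

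The figure is too high in every cell, and the excess grows with the share discharged alive.

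**4. SIC contrast.** The hazard ratio (SIC vs no SIC) is the ratio of the two H_D values. Example: deaths 35% vs 25%, discharge 20% vs 50%. SIC: −ln 0.45 × 0.35/0.55 = 0.508. No SIC: −ln 0.25 × 0.25/0.75 = 0.462. Ratio 1.10.

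| Deaths, SIC vs no SIC | Live discharge, SIC vs no SIC | Odds ratio of death | Hazard ratio, censored at discharge | Kaplan–Meier mortality |
|---|---|---|---|---|
| 40% vs 25% | 20% vs 50% | 2.00 | 1.32 | 45.7% vs 37.0% |
| 40% vs 25% | 20% vs 60% | 2.00 | 1.09 | 45.7% vs 42.8% |
| 35% vs 25% | 20% vs 50% | 1.62 | 1.10 | 39.8% vs 37.0% |
| 35% vs 25% | 20% vs 60% | 1.62 | 0.91 | 39.8% vs 42.8% |
| 30% vs 25% | 20% vs 50% | 1.29 | 0.90 | 34.0% vs 37.0% |
| 30% vs 25% | 20% vs 60% | 1.29 | 0.75 | 34.0% vs 42.8% |

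Every row shrinks the contrast. The direction changes only where the discharge gap is large relative to the mortality difference: a 5-point difference with a gap of 30 points or more, or a 10-point difference with a 40-point gap. With a 15-point difference it does not change in either case.

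**5. Log-rank by simulation** (375 vs 475 patients, 150 runs per case, two-sided 0.05 assumed because the article states no level; simulation error at most √(0.5 × 0.5/150) = 4 percentage points).

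- Deaths 35% vs 25%, discharge 20% vs 50%: SIC is found worse in about 15% of runs when discharge is censored, and in about 91% when patients discharged alive stay at risk to day 28.
- Deaths 30% vs 25%, discharge 20% vs 60%: censoring at discharge makes log-rank significant in favour of SIC in about 56% of runs.

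**6. Analyses that do not censor.** Proportions, χ² tests and logistic models count a patient discharged alive as a survivor. They return the true D in each group, so none of this applies to them.

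**The case against.** **Censoring at discharge is inferred.** The Kaplan–Meier sentence states no endpoint, time origin or censoring rule, and a full plan that is not shown may set one. Keeping discharged patients at risk to day 28 is compatible with the text. This stands as a limit on certainty. It does not remove the point, because the published outcome definition and the published method, taken together, lead by default to censoring.

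**Some follow-up to day 28 exists.** Section 2.5 has a day-28 check, and section 2.18 anonymises records only after the 28-day follow-up. But the day-28 check lists cardiovascular events, thromboembolism and bleeding, not vital status, and section 2.4 ends the mortality, thromboembolic and bleeding outcomes at discharge.

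**Log-rank with censoring at discharge is a valid test.** This is true for the cause-specific hazard of death. The error would be to present it as a comparison of mortality risk, or to read one minus Kaplan–Meier as that risk. A hazard ratio and an odds ratio for in-hospital death are also different quantities, so differing values are not in themselves a contradiction.

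**Stronger readings.** A reader might infer that the trial's 28-day mortality will be overstated in general. The documents do not support that: mortality is also reported as proportions and by logistic regression, and in-hospital figures miss deaths after discharge, so if anything they understate 28-day mortality. A reader might also infer that the SIC comparison is likely to reverse. With equal 30% mortality and discharge of 30% vs 60%, the hazard ratio would indeed be 0.60. But section 1 expects higher mortality with SIC, the article gives no discharge rates, and the adjusted SIC comparison is logistic and cannot reverse by this route.

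**Conclusion.** The point holds for the Kaplan–Meier curves and the unadjusted log-rank test, on the ordinary reading that live discharge is censored. The upward bias in the curves is certain in direction on that reading. Its size rests on assumed rates and constant hazards: about 4 to 15 percentage points at a true in-hospital mortality of 30% (34.0–45.3%). For the SIC contrast, attenuation is the general effect if SIC patients leave hospital more slowly; reversal is a special case.

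The outcome names also need to be aligned. A figure that stops at discharge is neither the 28-day survival of the abstract nor directly comparable with cohorts followed to day 28 regardless of discharge.

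Severity is moderate. The primary outcomes, SIC incidence and prevalence, are untouched, and the mortality outcome is secondary.

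**What to change.** **Section 2.10.** For in-hospital death by day 28, use cumulative incidence (Aalen–Johansen) with live discharge as a competing event, and Gray's test for group comparisons. Alternatively, keep patients discharged alive in the risk set to day 28; the day-28 estimate then equals the proportion who died in hospital. Do not read one minus Kaplan–Meier censored at discharge as mortality risk. If log-rank with censoring at discharge is kept, label it a comparison of cause-specific hazards among patients still in hospital.

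**Abstract, 2.4 and 2.5.** Use the single name 28-day in-hospital mortality, and limit the cohort comparison in 2.5 to in-hospital 28-day mortality of other cohorts.

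**Cost.** Changes of wording in the protocol and analysis plan, and a little extra analysis. Discharge date and status at discharge are already collected. The reported mortality will be lower than a Kaplan–Meier figure. The choice should be fixed before analysis. Section 2.18 makes the records fully anonymous after the 28-day follow-up, so vital status after discharge could not be added later.

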### 2.2. Eligibility Criteria

General patient data is collected from all adult patients treated in one of the participating intensive care units during the observation period (see Section 2.5). Patients are screened for sepsis on a daily basis. Patients are included in the detailed data collection if they fulfill all of the following criteria:The patient must be treated in a participating ICU.The patient must be ≥18 years of age.The patient must be diagnosed with sepsis or septic shock [2]:
Definition of sepsis: Acute suspected or confirmed infection plus a sepsis-induced increase in SOFA score by ≥2 points compared with baseline (last-documented value in the ICU or approximate baseline value in cases with known pre-existing conditions, e.g., documented SOFA impairment due to renal insufficiency, COPD, thrombocytopenia, or pre-existing brain damage). In cases where no pre-existing conditions are identified, the pre-existing SOFA score can be assumed to be “0”.Definition of septic shock: Sepsis plus persisting hypotension requiring vasopressors to maintain MAP ≥ 65 mm Hg plus lactate ≥ 2 mmol/L after an initial bolus volume of 30 mL/kg body weight (bw).

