A logistic regression model will be used to investigate mortality and describe it using odds ratios (including the associated 95% confidence intervals). Only variables that prove to be significant in the univariate analysis will be transferred to a multivariate model.

Multivariate logistic regression will be performed to compare the survival of SIC-positive and SIC-negative patients while adjusting for age, sex, the use of anticoagulants, and the SIC-adapted SOFA score at sepsis onset (i.e., the time of sepsis diagnosis). To calculate the SIC score, the SOFA score will be adapted according to Iba et al. [4] (see also Table 1). Two-sided *p* values will be used.

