**Figure 2 jcm-14-04222-f002:**
[figure not shown]
Overview of the timeline of the INSIC trial. SIC = sepsis-induced coagulopathy.

**Table 1 jcm-14-04222-t001:** Sepsis-induced and sepsis-associated coagulopathy scores.

SIC Score Iba et al. [4]			SAC Score Lyons et al. [6]
		Points	
Platelet count SIC subscore (PSSC) (platelet count (PLC) [1/nL]	>150/nL	0	**Mild SAC** 1.2 ≤ INR < 1.4 **and** 100 > PLC ≤ 150
	100 to <150/nL	1	
	<100/nL	2	
International Normalized Ratio (INR) SIC subscore (ISSC) [ ]		0	
	≥1.2 to <1.4	1	
	≥1.4	2	
SOFA subscore (truncated SOFA score, including the respiratory, cardiocirculatory, hepatic, and renal subscore) [Points]	0	0	
	1	1	
	≥2	2	**Moderate SAC:** 1.4 ≤ INR < 1.6 **or** 80 ≥ PLC ≤ 100;
No SIC		<4 points	**Severe SAC** INR ≥ 1.6 **or** PLC < 80
SIC		≥4 points (with PT-INR plus platelet count exceeding 2)	

ISSC = international normalized ratio (INR) SIC subscore; PLC = platelet count; PSSC = platelet sepsis-induced coagulopathy subscore; SAC = sepsis-associated coagulopathy; SIC = sepsis-induced coagulopathy; SOFA = sequential (sepsis-related) organ failure assessment.

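### The general mortality model screens covariates by univariate significance, and the severity term in the separate SIC comparison can be read as a 0–2 point item that would adjust for almost nothing

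*Protocol article*

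**What the plan says.** Section 2.10 (Statistical Methods) describes two logistic analyses of death in consecutive paragraphs.

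- **General mortality model.** "A logistic regression model will be used to investigate mortality and describe it using odds ratios". Covariates are chosen by a filter: "Only variables that prove to be significant in the univariate analysis will be transferred to a multivariate model".
- **SIC comparison.** "Multivariate logistic regression will be performed to compare the survival of SIC-positive and SIC-negative patients". The same sentence goes on to name the covariates of this model: "adjusting for age, sex, the use of anticoagulants, and the SIC-adapted SOFA score at sepsis onset". This list is fixed in advance and no filter is stated for it.

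For the adapted SOFA the section adds: "To calculate the SIC score, the SOFA score will be adapted according to Iba et al. [4] (see also Table 1"). The Table 1 item is labelled "SOFA subscore (truncated SOFA score, including the respiratory, cardiocirculatory, hepatic, and renal subscore"), with levels 0, 1 and ≥2 that earn 0, 1 and 2 points. SIC itself is "≥4 points (with PT-INR plus platelet count exceeding 2").

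Section 2.2 sets the sepsis entry criterion: "Acute suspected or confirmed infection plus a sepsis-induced increase in SOFA score by ≥2 points compared with baseline".

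**The concern.** **The filter.** A univariate p value is a poor test of whether a variable confounds. A confounder can look null on its own because another variable masks it, or because the sample is too small to show a moderate effect. A pure noise variable still enters 5% of the time at an assumed two-sided 0.05. The final odds ratios and intervals are then reported as if the model had been chosen beforehand.

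**The severity term.** Patients with SIC can be expected to be sicker, so the comparison of their survival depends on how well severity is adjusted for. A covariate that takes the value 2 in nearly everyone cannot do that. Table 1 is the only scoring of the adapted SOFA in the article, and Section 2.10 refers to it. The Discussion presents the study as a basis for planning later trials and takes up a possible causal role of coagulopathy in mortality. An association produced by severity alone would mislead that planning.

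**The anticoagulant term.** Section 2.5 records both pre-existing anticoagulation and doses given from day 0 onward. The covariate does not say which is meant. Doses given after SIC onset lie after the exposure.

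**Working it through.** **1. The data set, from Section 2.7.** The cited German study had about 1500 cases in 133 ICUs over 4 weeks. Scaled to 150 ICUs and 2 weeks: 1500 × (150/133) / 2 = 846, which reproduces the stated 850. SIC at 30–60% of 850 is 255–510, against the stated 250–500. These planning figures are sound, and N = 850 is used below.

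**2. How often the filter keeps a real risk factor.** Assumptions not in the article: factor present in 20% (170 against 680 patients), 33% mortality without it, two-sided 0.05.

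- Mortality with the factor: p1 = OR × 0.4925 / (1 + OR × 0.4925), where 0.4925 = 0.33/0.67.
- Chance of passing: Φ[(p1 − 0.33 − 1.96 × SE0) / SE1], with SE0 pooled and SE1 unpooled.
- Worked case, OR 1.3: p1 = 0.390, difference 0.0604, SE0 = 0.0407, SE1 = 0.0415. This gives Φ(−0.47) = 0.32. With the unpooled error throughout it is 0.31.

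| True OR | p1 | Chance of entering the model |
|---|---|---|
| 1.2 | 0.371 | 18% |
| 1.3 | 0.390 | 32% |
| 1.5 | 0.425 | 64% |
| 1.8 | 0.470 | 92% |

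**3. Whether the filter is needed to save parameters.** At an assumed 25–40% mortality, 850 patients give 850 × 0.25 = 212 to 850 × 0.40 = 340 deaths. At the customary 10 events per parameter, that supports roughly 20–30 prespecified parameters.

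**4. The SOFA item in the SIC comparison.** Entry requires a rise of at least 2 in total SOFA. The Table 1 item counts four organs. A patient scores below 2 on it only if the qualifying points come largely from the components left out (coagulation, nervous system). The item is also part of the exposure. The SIC-positive point combinations (platelets, INR, SOFA) are (1,2,1), (1,2,2), (2,1,1), (2,1,2), (2,2,0), (2,2,1) and (2,2,2). At the cap, SIC status is therefore decided by platelets and INR alone.

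**5. Size of the residual confounding if the 0–2 item is used.** In both simulations the true SIC odds ratio is 1 and all slopes and SOFA distributions are assumed.

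- *Setting A.* N = 300,000; SOFA a rounded gamma with mean about 6; logit P(SIC) = −1.6 + b(SOFA − 5) with b = 0.10 or 0.20; logit P(death) = −1.0 + 0.22(SOFA − 5). About 97% of patients are at the cap. At SOFA 6, P(SIC) is 1/(1 + e^1.5) = 0.18 to 1/(1 + e^1.4) = 0.20, below the protocol's 30–60%.
- *Setting B.* N = 850; SIC share 30% or 60% as in the protocol; mortality 35%; odds ratio per SOFA point 1.1 or 1.2; SIC liability shift 0.3 or 0.6 per SD of SOFA; 300 runs per combination. About 96% are at the cap.

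| SIC odds ratio (truth 1.0) | Setting A | Setting B | True null rejected (B) |
|---|---|---|---|
| Crude | 1.27–1.64 | 1.11–1.47 | 9–69% |
| Adjusted for the 0–2 item | 1.25–1.60 | 1.10–1.43 | 8–64% |
| Adjusted for the uncapped four-organ sum | 0.99–1.02 | 0.98–1.01 | 4–8% |

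The capped item moves the estimate by only a few hundredths from its crude value.

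**The case against.** **The two models are separate.** A reader might infer that the univariate filter leaves the SIC–mortality association confounded. The article does not support that. The filter sentence belongs to the general model, while the SIC comparison has named covariates and no p-value selection. This stands in full.

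**The cap is one reading.** Table 1 has a level of ≥2, so the truncated SOFA behind it can exceed 2 and only the points awarded for it are capped. The SIC-adapted SOFA could therefore mean the four-organ sum. On that reading the simulated bias vanishes. This also stands. A reader might conclude that the SIC odds ratio is bound to be confounded, but the text shows only that it would be if the 0–2 item is used. The cross-reference to Table 1 keeps that reading plausible.

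**Near-constancy is not a strict deduction.** The entry rule concerns total SOFA, and the article gives no distribution of the four-organ sum. The 96–97% at the cap is assumption-dependent.

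**The simulations fix the SIC effect at zero.** They show what bias is possible. They do not show that a real SIC association would be mostly severity.

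**These are secondary analyses.** The primary outcomes are incidence and prevalence, and Section 2.10 makes no causal claim for the odds ratio. True, and it limits the weight of the point.

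**Anticoagulant timing is mostly missing detail.** It may well be settled in the full protocol or analysis plan. It is worth a clause in the same edit and is not an error in itself.

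**Conclusion.** Two narrower points hold.

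1. The univariate filter in the general mortality model is an explicit rule and a weak one. Under the stated assumptions it omits a true factor with an odds ratio of 1.3 about two times in three, and one of 1.5 about one time in three. The expected number of deaths does not call for such a filter.
2. The severity covariate in the SIC comparison is ambiguous. If it is the 0–2 item of Table 1, adjustment is probably close to empty, and severity alone could produce an SIC odds ratio of about 1.1–1.6. If it is the uncapped sum, the simulated estimate is about 1.0. The range depends on the assumed SOFA distributions and slopes. That a nearly constant covariate adjusts for almost nothing does not depend on them.

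The primary outcomes are unaffected. The changes should be made because these are analyses the article commits to and the cost is very small.

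**What to change.** - **General mortality model.** Replace the filter sentence with a covariate list chosen on subject-matter grounds, all terms kept regardless of p value. For example: age, sex, admission type, infection focus, severe liver disease, pre-existing anticoagulation or antiplatelet therapy, and the non-coagulation SOFA sum at sepsis onset.
- **SIC comparison, severity.** State that the covariate is the uncapped four-organ (or non-coagulation) SOFA sum at sepsis onset, entered as a continuous variable, and not the 0–2 points of Table 1. Leaving out the coagulation component keeps platelets, which define SIC, out of the adjustment.
- **SIC comparison, anticoagulants.** Define the covariate as therapy already in place at sepsis onset.

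The cost is wording only. Section 2.5 already collects SOFA on the day of sepsis diagnosis and the other variables listed. The one downside is a few more parameters in the general model, which the expected number of deaths can carry.
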